#### Follow-up 1: SSS engagement

After women have consented and been informed of their group allocation, trial research staff will contact their local SSS to ascertain whether women attended a first appointment with an SSS advisor and set a quit date. This information will be entered into the trial database for both control group and intervention group women. A £50 voucher will automatically be dispatched to intervention group women who attended and set a quit date.

#### Follow-up 2: 4 weeks post quit date

For those women who engaged with the SSS and set a quit date, trial research staff will contact their local SSS 4 weeks after this quit date to obtain their smoking status in the last 2 weeks and CO breath test result as recorded by the SSS. Where a breath test result is not available from the SSS trial, research nurses will collect this directly from the woman for the incentives group to initiate incentive payments. CO breath test results will be collected for the control group only where these are available from the SSS in line with national SSS guidelines. This information will be entered onto the trial database. If the CO result is at or below the accepted level for a non-smoker at the site, a £50 voucher will automatically be dispatched to women in the incentives group.

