**Fig. 1 Fig1:**
[figure not shown]
Overview of the trial design and flow of participants through the study. *CO = expired carbon monoxide. CO validated quit = CO less than or equal to 5 ppm (site dependent to dovetail with local SSS cut-off point)

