#### Secondary outcomes

Secondary outcomes include other key smoking cessation, child, health economic and process endpoints, and focus on the difference between the intervention and control groups regarding the following:
Proportion of women who engage with SSS (locally defined) and set a quit dateProportion of women with biochemically validated (CO) self-reported abstinence from smoking for at least 14 days at 4 weeks after quit dateProportion of women with cotinine/anabasine-verified self-reported point abstinence from smoking for at least 8 weeks at 6 months post-partumProportion of women with cotinine/anabasine-verified self-reported continuous abstinence from smoking from late pregnancy to 6 months post-partumMean difference in birth weightCost-effectiveness: incremental cost per late pregnancy quitter and cost per quality-adjusted life year (QALY) gained over the trial time horizon and lifetimeProcess evaluation: barriers and facilitators to trial recruitment and future implementation of incentives in practice

Data for the primary outcome and secondary outcomes 1, 2 and 5 will be combined with data from the feasibility trial in a meta-analysis, as described in ‘Statistical methods’.

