#### Secondary outcome analysis

Engagement with SSS and self-reported smoking status at 4 weeks will both be analysed using a logistic regression model adjusting for the same covariates as the primary analysis. Continuous and point abstinence (i.e. regardless of whether participants were abstinent in late pregnancy) outcomes obtained at 6 months post-partum [28] will be calculated using logistic regression also adjusting for the same covariates as the primary outcome analysis. For each of the following covariates, tests for interaction with the treatment group will be performed: age of mother, years of smoking, deprivation score and level of smoking. Effects on the length of neonatal unit stays will be examined.

Birth weight will be analysed using a linear regression model adjusting for key prognostic variables including age, site, height and weight of mother at early pregnancy. The intention-to-treat estimate will be severely diluted due to low smoking cessation rates and the ‘per protocol’ analysis will be biased by confounding. Consequently, we will also utilise an instrumental variable approach—complier average causal effect analysis—which will estimate the true impact of incentive-induced smoking cessation on birth weight [35].

Differences by subgroup (e.g. site, deprivation, age group) will be explored and reported as per the CHAMP guidelines [36].

A meta-analysis including data collected in the feasibility study in Glasgow on 612 participants [24] will be undertaken.

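### At 4 weeks, missing CO readings are chased in the incentives arm only; if the CO-validated endpoint is analysed, this favours incentives, and the analysis section names a different endpoint

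*Protocol article*

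**What the plan says.** Under Secondary outcomes, the second outcome is the proportion of women with "biochemically validated (CO) self-reported abstinence from smoking for at least 14 days at 4 weeks after quit" date, compared between the intervention and control groups. The same section sends it to the pooled analysis: "Data for the primary outcome and secondary outcomes 1, 2 and 5 will be combined with data from the feasibility trial in a meta-analysis".

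Under Follow-up 2, smoking status and the CO result for women who set a quit date are taken from the local SSS. When the SSS has no breath test, the two arms part. In one, "research nurses will collect this directly from the woman for the incentives group to initiate incentive payments". In the other, "CO breath test results will be collected for the control group only where these are available from the SSS", which the article ties to national SSS guidelines.

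Under Secondary outcome analysis, the endpoint to be modelled is worded differently: "Engagement with SSS and self-reported smoking status at 4 weeks will both be analysed using a logistic regression model".

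The Missing data section counts women with unknown status as smokers for the primary outcome and for the 6-month smoking outcome. It states no such rule for the 4-week outcome.

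**The concern.** Take two women with the same smoking behaviour, both abstinent at 4 weeks and neither with an SSS breath test. The one in the incentives arm can still become a validated quitter through a nurse visit; the one in the control arm cannot. Ascertainment then depends on allocation, and the difference lies in a collection rule. Covariate adjustment cannot recover control readings that were never taken.

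At stake are the between-arm comparison of one secondary outcome and its pooled version with the feasibility trial. Separately, the outcome section and the analysis section name different 4-week endpoints, so the article does not settle whether this asymmetry enters the analysis.

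**Working it through.** **The plan's own figure.** The only sample-size figure is for the primary outcome: 7% against 14%, 90% power, two-sided 5%, 15% loss, 470 per arm. The pooled-variance formula without continuity correction gives 401 per arm; 401/0.85 = 472 per arm, 944 in total. The unpooled formula gives 936. The stated 940 reproduces and is not touched by this point. The article gives no figure for the 4-week outcome.

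**Inputs for the check.**
- From the article: 470 per arm, 1:1 allocation, two-sided 5% tests, and the two CO collection rules in Follow-up 2.
- Assumed, because the article does not give them: q, the true 4-week quit rate among all randomised women, equal in both arms (10%, 15%, 20%); u, the share of quitters without an SSS CO reading, equal in both arms (10%, 20%, 30%); r, the share of those recovered by nurses in the incentives arm (50%, 80%, 100%).
- Also assumed: a quit without a CO reading counts as not quit.

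**Formulas.**
- Expected control rate: pC = q(1 − u).
- Expected incentives rate: pI = q(1 − u + ur).
- Spurious difference: d = qur. Spurious risk ratio: (1 − u + ur)/(1 − u), which does not depend on q and exceeds 1 whenever u and r are above zero.
- Rejection probability with n = 470: Φ((d − 1.96·se0)/se1) + Φ((−d − 1.96·se0)/se1), where se0 = √(2p̄(1 − p̄)/n), p̄ = (pC + pI)/2 and se1 = √((pC(1 − pC) + pI(1 − pI))/n).

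**One case in full.** With q = 15%, u = 20%, r = 80%: pC = 0.15 × 0.80 = 0.120; pI = 0.15 × (0.80 + 0.16) = 0.144; d = 0.024; risk ratio 0.144/0.120 = 1.20. Then p̄ = 0.132, se0 = 0.0221, se1 = 0.0221, and the rejection probability is Φ(−0.87) + Φ(−3.05) ≈ 0.192.

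**Spurious risk ratio with no true effect.**

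| r | u = 10% | u = 20% | u = 30% |
|---|---|---|---|
| 50% | 1.06 | 1.125 | 1.21 |
| 80% | 1.09 | 1.20 | 1.34 |
| 100% | 1.11 | 1.25 | 1.43 |

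**False-positive rate (nominal 5%).**

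| q | r | u = 10% | u = 20% | u = 30% |
|---|---|---|---|---|
| 10% | 50% | 5.8% | 8.5% | 13.8% |
| 10% | 80% | 7.0% | 13.9% | 26.8% |
| 10% | 100% | 8.2% | 18.8% | 37.8% |
| 15% | 50% | 6.3% | 10.6% | 18.9% |
| 15% | 80% | 8.3% | 19.2% | 39.0% |
| 15% | 100% | 10.1% | 27.0% | 54.3% |
| 20% | 50% | 6.8% | 12.9% | 24.6% |
| 20% | 80% | 9.6% | 25.1% | 51.1% |
| 20% | 100% | 12.2% | 35.8% | 68.8% |

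The spurious difference runs from 0.5 percentage points (0.10 × 0.10 × 0.50) to 6.0 points (0.20 × 0.30 × 1.00).

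**With equal ascertainment.** If the same CO source counts in both arms and SSS recording is equally complete, pC = pI, the risk ratio is 1.00 and the rejection rate returns to 5%.

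How far the pooled estimate would move cannot be computed, because the article does not give the feasibility trial's 4-week data or say how its CO readings were obtained.

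**The case against.** The strongest reply is that the bias may never enter the analysis. The section that says how the 4-week outcome is modelled names self-reported status, and Follow-up 2 takes that status from the SSS for women in both arms who set a quit date. On that reading only the CO back-up differs by arm, and most of the bias goes. This stands, so the bias is conditional. What remains on that reading is that the declared endpoint is not the one analysed.

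The direction also needs a rule for missing CO that the article does not state for 4 weeks. If women without CO were excluded rather than counted as not quit, the direction would be undetermined. This too stands, and the detailed rule may be in the analysis plan, which is not at hand.

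Nurse readings have a stated operational purpose, to start voucher payment, in a pragmatic trial against usual support. That justifies taking them. It does not justify counting them as outcome data in one arm only.

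A reader might go further than the article allows in four ways:
- *That the 4-week result favours incentives whatever the truth.* This does not follow, for the two reasons above. The highest false-positive rates also need the least favourable assumptions together: a 20% quit rate and complete nurse recovery.
- *That the trial's main conclusion is compromised.* It is not. Cotinine or anabasine follow-up in late pregnancy and at 6 months post-partum covers both arms by the same procedure.
- *That the CO cut-off, described in the Fig. 1 legend as "site dependent to dovetail with local SSS cut-off point", adds bias between arms.* Allocation is individual, the cut-off applies to both arms within a site, and the model adjusts for site. A common cut-off would be a preference.
- *That the expectation of few missing data in other secondary outcomes is contradicted.* That sentence is general, with birth weight as its example, and no rate of missing CO is given. The contradiction is not shown.

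**Conclusion.** The arm-specific CO back-up is explicit, nothing in the article equalises it, and the outcome and analysis sections disagree on the 4-week endpoint. Those three facts are certain.

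The bias holds if the CO-validated definition governs and a quit without CO counts as not quit. It then favours incentives under no effect and would carry into the pooled 4-week estimate. Its size rests on three quantities that the article does not give; the ranges in the brief and tables are illustrations, not estimates. A middle case (15% quitting, 80% recovery) gives false-positive rates of about 8%, 19% and 39% as the share without SSS CO rises from 10% to 20% to 30%.

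This should be corrected before analysis. It concerns one secondary outcome and its meta-analysis, and leaves the primary and 6-month outcomes alone.

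**What to change.** 1. Reconcile the Secondary outcomes and Secondary outcome analysis sections so that both name one 4-week endpoint.
2. Flag the source of each CO reading (SSS or research nurse) in the database.
3. For the between-arm comparison and the meta-analysis, count only SSS-recorded CO in both arms. Keep nurse readings for voucher payment.
4. Use all randomised women as the denominator, with missing counted as smoking in both arms.
5. Report SSS-recorded self-reported 14-day abstinence as a companion analysis.
6. Report the availability of SSS CO readings by arm.

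The cost is a source flag and some wording; no new data collection and no change to vouchers. There are two downsides. The validated rate in the incentives arm will look lower, because nurse-confirmed quits no longer count in the comparison. And SSS-only CO may still differ by arm if vouchers, or the existence of nurse back-up, change whether the SSS takes a reading; item 6 is there to show this. Nurse back-up in both arms would also equalise collection from now on, but the Trial status section reports 837 of 940 women (89%) enrolled by 17 December 2019, so it would come late for most.

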#### Follow-up 3: 12 weeks post quit date

For those women in the intervention group who were confirmed quit at 4 weeks, trial research staff will contact their local SSS 8 weeks later to obtain their smoking status and CO breath test result as recorded by the SSS. Where this is not available from the SSS trial, research nurses will collect this directly from the woman. This information will be entered into the trial database. If the CO result is at or below the accepted level for a non-smoker at the site, a £100 voucher will automatically be dispatched

#### Follow-up 4: late pregnancy (34–38 weeks gestation)

All women will be followed up at the primary outcome stage in late pregnancy. Follow-up telephone contact will be attempted by the TCC at a random date between 34 and 38 weeks gestation allocated at the time of initial randomisation. Trial research nurses will review the women’s notes 1 week prior to the telephone contact to check the health status of mother and baby and to alert TCC staff to any adverse events (e.g. miscarriage or stillbirth) that may require particular sensitivity when conducting follow-up. TCC staff will be blind to group allocation.

Three attempts will be made by the TCC to contact women. If no contact is established women will be followed up by local research staff by telephone, text and letter. On successful contact, women will be asked ‘Have you smoked in the last 8 weeks?’ If yes, ‘Have you smoked more than 5 cigarettes in that time?’ EQ-5D-5L data [33] and current NRT/electronic cigarette use will also be collected at this time point.

Self-report of not smoking will be corroborated by cotinine estimation on saliva or urine (when saliva collection cannot be tolerated). Where women are also using NRT or electronic cigarettes, anabasine assay on urine will replace cotinine. Cotinine and anabasine will be assayed by ABS Laboratories Limited. To minimise the potential for women to ‘game’ the primary outcome, incentive payments will be dependent on the CO result, which is an immediate measure, and not on the cotinine or anabasine level.

An important aspect of the primary outcome for this phase III trial is the proportion of women successfully followed up in both the intervention and control groups. To minimise loss to follow-up, particularly among controls, women in both groups will receive Love2Shop vouchers of £50 and £25 for providing data and saliva/urine samples where applicable at the primary (late pregnancy) and secondary (6 months post-partum) outcome time points, respectively (Fig. 2). Acceptable levels are around 90% of participants successfully followed up in each group.

To assess whether women lost to trial follow-up are still smoking towards the end of pregnancy and whether the primary outcome has been ‘gamed’ (saliva cotinine below the cut-off point but still smoking in late pregnancy), residual blood from routine late pregnancy samples, where available, will be tested.

#### Follow-up 5: 6 months post-partum

Similar to the late pregnancy follow-up, all women will be contacted at 6 months after their expected delivery date to ascertain their smoking status and collect a saliva/urine sample for those women who self-report as quit. Quit status 6 months after birth will be ascertained by two sets of questions:
‘Have you smoked in the last 8 weeks?’ If yes, ‘Have you smoked more than 5 cigarettes in that time?’‘Have you smoked since your baby was born?’ If yes, ‘Have you smoked more than 5 cigarettes in total since your baby was born?’

Follow-up procedures (i.e. number of contact attempts, data collection and saliva/urine sample collection and assay) will be the same as those described for the late pregnancy follow-up. Biological samples of saliva and urine will not be available for use by other researchers.

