#### Adherence with intervention

Women allocated to the intervention group will have the opportunity to receive shopping vouchers at four key time points in the trial, dependent on their smoking status. Consequently, adherence will be assessed by considering distribution and receipt of shopping vouchers, which will be confirmed by Royal Mail signature.

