### Outcomes

#### Primary outcome

The primary outcome is cotinine/anabasine-verified abstinence from smoking for at least 8 weeks towards the end of pregnancy at 34–38 weeks gestation. The proportion of abstinent women will be compared between the intervention and control groups.

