### Participant timeline and data collection

The trial consists of an intervention phase between 6 and 38 weeks gestation with five assessment points and follow-up to 6 months post-partum. The total study period for each participant will be 42–62 weeks dependent on gestation at enrolment and timing of primary outcome assessment in late pregnancy (randomised between 34 and 38 weeks gestation). See Fig. 1 for an overview of the study design and measurement time points, and Fig. 3 for the schedule of assessment and data collection.

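### The continuous-abstinence outcome starts in late pregnancy, but no described question covers the weeks from that contact to birth

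*Protocol article*

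**What the plan says.** The fourth item under Secondary outcomes in the Protocol article is verified, self-reported abstinence that runs without interruption from late pregnancy to 6 months after birth.

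The start point is the late-pregnancy assessment. The Primary outcome section defines it as "abstinence from smoking for at least 8 weeks towards the end of pregnancy at 34–38 weeks gestation". Under Follow-up 4, "Follow-up telephone contact will be attempted by the TCC at a random date between 34 and 38 weeks gestation", and the smoking question put to women there concerns the preceding 8 weeks.

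The end point is set out under Follow-up 5: "Quit status 6 months after birth will be ascertained by two sets of questions". The first set opens with "Have you smoked in the last 8 weeks". The second opens with "Have you smoked since your baby was born" and, if the answer is yes, continues with "Have you smoked more than 5 cigarettes in total since your baby was born". Self-reported quitters give saliva or urine at that time.

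The section on birth-related data lists parity, the birth date and the birth weight, but no smoking status.

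**The concern.** The outcome is named for one interval and the questions cover another. One question looks back from 34–38 weeks, one looks back 8 weeks from the 6-month call, and one starts at birth. The weeks from the late-pregnancy contact to delivery belong to the outcome by definition, yet no described question asks about them.

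A woman who was verified abstinent at, say, 35 weeks, smoked in the following weeks, and then stopped at birth would be counted as continuously abstinent. What is at stake is the meaning of one secondary result. A reader would take it as unbroken abstinence from late pregnancy, when it shows abstinence in two separate windows. An analysis plan could not repair this, because it cannot recover an interval that nobody was asked about.

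**Working it through.** **The plan's own figure.** The article gives no figure for this outcome. Its sample size rests on the primary outcome: 7% against 14%, two-sided 5% level, 90% power, 15% loss. With unpooled variance, n per arm = (1.960 + 1.282)² × (0.07 × 0.93 + 0.14 × 0.86) / 0.07² = 398. Then 398 / 0.85 gives 469 per arm, or 938 in total. The pooled form gives 401, then 472 per arm, or 944. The stated 940 is reproduced and is not touched by this point.

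**Step 1: the windows side by side.**

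- Outcome as named: late-pregnancy assessment to 6 months post-partum.
- Late-pregnancy question: the 8 weeks before the contact at 34–38 weeks.
- First 6-month question set: the 8 weeks before the 6-month call.
- Second 6-month question set: birth to the 6-month call.
- Not covered: late-pregnancy contact to birth.

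Two biological measures do not fill the gap. The 6-month sample cannot verify an interval that ended months before. The residual blood described under Follow-up 4 serves to check women lost to follow-up and possible gaming of the primary outcome. It is not described as feeding this one.

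**Step 2: length of the gap.** Gap = gestation at birth − gestation at the late-pregnancy contact. Assumptions: birth at 40 weeks, 6 months = 26 weeks, contact on the scheduled date.

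- Contact at 34 weeks: 40 − 34 = 6 weeks, and 6 / (6 + 26) = 19% of the named interval.
- Contact at 36 weeks: 40 − 36 = 4 weeks, and 4 / 30 = 13%.
- Contact at 38 weeks: 40 − 38 = 2 weeks, and 2 / 28 = 7%.

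For births at 37–42 weeks the gap runs from none (birth at or before the contact) to 42 − 34 = 8 weeks. A contact made later than scheduled shortens it.

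**Step 3: who is misclassified.** All of these must hold: verified abstinent in late pregnancy; smoked between that contact and delivery; smoked no more than 5 cigarettes from birth to 6 months; verified again at 6 months. (This reads the 5-cigarette follow-up question as the tolerance.) The gap cannot wrongly remove anyone, so this error only raises the rate.

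**Step 4: possible size, by assumption only.** The documents give no relapse figures. Suppose that 10–30% of late-pregnancy quitters smoked in the gap and that 2–20% of those were then abstinent from birth to 6 months. The misclassified share is between 0.10 × 0.02 = 0.2% and 0.30 × 0.20 = 6% of late-pregnancy quitters. At the planning quit rates:

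- Intervention: 470 × 0.14 = 65.8 quitters, so 0.1 to 3.9 women, or 0.03 to 0.84 percentage points.
- Control: 470 × 0.07 = 32.9 quitters, so 0.07 to 2.0 women, or 0.01 to 0.42 points.

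The sample size section says that only the first 75% of recruits will be followed to 6 months. The upper counts then become 3.9 × 0.75 = 2.9 and 2.0 × 0.75 = 1.5 women.

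If the same share of quitters is misclassified in both arms, the difference between arms rises by at most 0.84 − 0.42 = 0.42 points. The ratio does not move if the arms retain quitters equally well.

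**The case against.** The strongest reply is that the gap lets little through. A woman who relapses before delivery and goes on smoking is caught by the since-birth question. Misclassification needs a relapse and then a new quit at birth that lasts about 6 months. The Need for a further trial section names relapse after birth as the main uncertainty, and the since-birth question addresses exactly that. Birth is also a firmer anchor for recall than a telephone call months earlier. All of this stands, and it is why the point is minor.

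A reader might go further and infer a bias in favour of incentives. Intervention women "will have the opportunity to receive shopping vouchers at four key time points in the trial, dependent on their smoking status", and the timeline says "The trial consists of an intervention phase between 6 and 38 weeks gestation with five assessment points and follow-up to 6 months post-partum". The unasked weeks therefore follow the end of abstinence-contingent payment in one arm only, and relapse set off by its withdrawal might seem to be missed mainly there. The documents do not support this. Relapse that continues past birth is detected, and nothing in the described payments explains a new quit at birth. Women in both arms face the same unasked weeks, and no information is given on misclassification by arm.

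A last reply is that a journal article condenses the full protocol, and that the schedule of assessments (Fig. 3) is not shown. A further question elsewhere cannot be excluded. But the article prints the questions and says that quit status at 6 months is ascertained by them, so the mismatch lies in what is stated, not in what is left out.

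**Conclusion.** The point holds as a mismatch between the name of a secondary outcome and the questions that measure it. The error can only be upward. Its size cannot be computed from the documents and is probably small. Under the assumed shares it stays below 1 percentage point in either arm, and those shares have no source in the article. A difference between arms is neither shown nor excluded. The gap length rests on the assumed gestation at birth and on contact at the scheduled date. The severity is low.

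**What to change.** Define and report the outcome as *abstinent in late pregnancy and from birth to 6 months post-partum*. This costs only a change of label and states what was measured for every woman.

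Optionally, for 6-month calls still to be made, add one question on smoking between the late-pregnancy contact and the birth. Keep the since-birth item as the common definition for all women, and report the full-interval version as a supplementary result. The Trial status section reports 837 of 940 women enrolled on 17 December 2019, and each woman's study period is at least 42 weeks, so some of these calls were then still to come.

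The cost is one line in the call script. The downside is that the full-interval version exists only for later calls and relies on longer recall, so it should not replace the common definition.
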